### Data management

Data including the screening survey, online survey, time-use survey, accelerometer log, and in-person health assessment data collection form will be entered into Qualtrics, a secure data capture system. The data system includes password protection and internal quality checks, such as automatic range checks, to identify data that appears inconsistent, incomplete, or inaccurate. Paper copies of any forms and logs will be stored in a safe cabinet with a lock located at a secure research center. For data captured as part of the online dietary recall, we will utilize the ASA24 system, which comprises a secure database where responses are encrypted during transmission using Secure Socket Layer (SSL) technology.

### Data analysis

For Aim 1, we will compare the changes in physical activity outcomes (moderate to vigorous physical activity [MVPA], light, moderate, and vigorous physical activity [LMVPA], walking, sedentary behavior) between the agrihood and comparison participant groups across three time points (Agrihood: pre-move-in, 3 months after move-in date, 6 months after move-in date; Comparison: 0, 3, 6 months) using DiD analysis (linear mixed-effects longitudinal models). Regression models will include the group, time period, and the group by time period interaction terms. Random cluster effects will be included to account for correlations between participants in the same neighborhood and *a priori* covariates of age, sex, and educational attainment. Random effects for the participants will be included to account for correlation in observations. To address multicollinearity, we will assess variance inflation factors (VIF > 5) and pairwise correlations (|r| > 0.70); collinear variables will be excluded, combined, or tested in sensitivity analyses to avoid attenuation of the group × time effect. Confounders showing baseline imbalance (standardized mean difference > 0.10) will be prioritized for inclusion. Restricted maximum likelihood will be used for complete case analysis to incorporate all available data, and intention-to-treat analysis will include all participants included at baseline. Multiple imputation will be used to estimate missing data points and standard errors. Imputations will follow standardized procedures, including auxiliary variables, and will follow hierarchical approaches. We will examine the potential for missingness of data to not be at random by comparing baseline characteristics of participants who have completed physical activity data with those who do not. If there are differences by age, education, race, or self-reported perceived health, any variables that differ will be used as an auxiliary variable in multiple imputation. Fraction of missing information will be used to measure level of uncertainty about the values imputed for missing values. We will use a number of imputations that satisfy the recommendation to have the number of imputations (at least) equal the highest fraction of missing information (FMI) percentage. Using the geographic information system (GIS) data and resulting maps, for physical activity resources we will: (1) count the number of resources located within the 5-mile network buffer using ArcGIS; (2) measure the distances to the closest resources for different types of resources (e.g., closest park or trail) using ArcGIS and Google Distances API; (3) assess how these counts and distances change over time; and (4) assess changes in time spent in transportation to go to resources. Specifically, we will compare the changes in number of physical activity resources, distance (in miles) to closest objectively measured resources, and distance (in miles) to utilized resources and associated transportation-related time spent between the groups across 3 time points (Agrihood: 0, 3 months after move-in date, 6 months after move-in date; Comparison: 0, 3, 6 months) using DiD analysis, and assess if any of these variables are associated with device-measured physical activity outcomes using linear mixed-effects multilevel models. All statistical analysis will be conducted using SAS and/or R software. We will also generate maps showing changing patterns in physical activity resource utilization in ArcMap. This two-pronged approach of mapping and analyzing objective physical activity environments as well as physical activity resource utilization and time use behaviors are important to better understand how the built environment in these communities are or are not conducive to physical activity, as well as how participants are (or are not) engaging in the resources designed to promote physical activity.

We will use the same strategy above to compare changes in food sourcing and dietary intake between groups across 3 time points (Agrihood: 0, 3 months after move-in date, 6 months after move-in date; Comparison: 0, 3, 6 months) using DiD analysis. MEPA-16 score will serve as the main dietary intake outcome for all participants, while ASA-24 nutrient and food group data will be examined among the Agrihood subsample. We will also compare the changes in number of food resources (by type), distance (in miles) to closest objectively measured food resources, and distance (in miles) to utilized food resources and associated changes in time spent in transportation to food resources between the groups across three time points (Agrihood: 0, 3 months after move-in date, 6 months after move-in date; Comparison: 0, 3, 6 months) using DiD analysis. We will assess if any of these variables are associated with dietary intake using linear mixed-effects multilevel models, with MEPA-16 score as the main outcome of interest. We will generate maps showing changing patterns in food resource utilization in ArcMap. Similar to the physical activity built environment, this approach of mapping and analyzing objective food resource environments, food resource utilization, and time use behaviors can help better understand how the built environment in these communities are or are not conducive to improving food access, connection to agriculture, and healthy eating, as well as how participants are (or are not) engaging in the resources designed to promote connection to agriculture and healthy eating.

In addition, we will explore the impact of social connection and loneliness on physical activity and healthy eating using the same DiD analyses but including social connection and loneliness terms into each of the regression models. We will analyze the survey data for loneliness and social connection over time using random effects models to assess change, and determine factors related to the changes. Additionally, we will explore mediation models using the changes in loneliness/connection scores as mediators for physical activity and dietary intake changes, using methods for analysis of mediation in generalized linear models.

For Aim 2, as described for Aim 1, we will use DiD analysis to explore longitudinal changes for residential time use and engagement outcomes (i.e., assess consumer preferences for built and nature design features). Self-report commuting time and time spent outside of the agrihood will also be measured to create dose measures for overall time spent in the neighborhood. Comparison participants will be asked about the time they spend engaging in features of their neighborhoods to allow for comparisons.

For Aim 3, an exploratory economic benefits analysis will be conducted using monetized data collected from participants (as part of Aims 1 and 2) accompanied by financial data and survey measures gathered from the developer. In regard to analysis of the resident data, descriptive analysis of demographics will be coupled with a thematic analysis of responses to open-ended questions asking residents to rate their perceived importance of the working farm, open-space views, trail networks, school quality, and other standard amenities, and price premiums they believe they will pay for these. This analysis will also examine estimated monthly expenditures on farm products compared to spending at conventional grocery stores or farmers’ markets; hypothetical willingness-to-pay to retain farm amenities; anticipated influence of the farm on diet, outdoor activity, sense of community, and children’s environmental awareness; understanding of any farm-related HOA fees and decision-making processes; and perceived risks and desires. Findings will yield comparable metrics for future cross-case analyses across agrihoods, linking residents’ expectations and preferences based on their open-ended responses, to community-level economic outcomes gathered from the developer survey.

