### Study aims and approaches

The specific aims for the *Neighborhood & Health Study* are to: (1) assess short-term changes in dietary intake, physical activity, cardiometabolic health indicators, and social connectedness among Texas residents living in the agrihood compared to non-agriculturally-integrated, master-planned neighborhood; (2) document time use with features of the agrihood and assess preferences for built and nature design features to provide resident-driven data for future developments; and (3) examine the resident- and community-level economic benefits of the agrihood.

The study design and selection of measures are guided by the socioecological model, which recognizes that health behaviors are influenced by interacting individual (e.g., diet, physical activity, stress), interpersonal (e.g., social connection), organizational (e.g., community programs), and environmental (e.g., built and natural design features) factors (27). This framework provides a foundation for examining how agrihood design features may affect resident health and wellbeing.

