##### Sample size estimation

Power was computed for a natural experiment evaluation (NEE) using Difference-in-Difference (DiD) analysis. For Aim 1, we calculated sample size for a Type I error rate alpha of 0.05, power of 0.8 for comparing the means between two groups considering physical activity outcomes of moderate-to-vigorous physical activity (MVPA); light, moderate, and vigorous physical activity (LMVPA); and time spent in sedentary behavior. Prior research has shown observed effects of moving to an activity-friendly community ranging between 10.4–10.9 min/day of MVPA, indicating small effect sizes of 0.40–0.42 (Cohen’s D) (7). We conservatively powered this study to detect a smaller effect size (Cohen’s D = 0.35). We estimate a sample size of 129 per group will provide adequate power to detect an effect size of Cohen’s D = 0.35 for all physical activity outcomes. The effect size of 0.35 is a conservative estimate based on current literature, equating to minimal detectable differences between 7.9 and 9.6 min/day for MVPA using estimates of standard deviation from previous studies (7, 33–37). This sample size is also adequate for a minimal detectable difference of 13.3 min/day for LMVPA. This sample size is adequate to detect effect sizes that are small to medium for all outcomes based on calculations for other aims. Prior community sampling of an NEE examining accelerometer-measured MVPA found a 20.64% attrition rate from baseline to year 1 and a 6.63% attrition rate from year 1 to year 2 (33). Given recently reported challenges to NEE recruitment, we conservatively overestimate attrition rates, necessitating a sample size of 175 for the agrihood and comparison groups.

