Our study design has several strengths, including multiple matched cohorts of residents. In addition, we propose a strong data-driven approach involving biological data collection from the mobile health assessment clinics and device-captured physical activity, along with highly valid and reliable self-report measures that capture individual and community-level preferences and perspectives. Given our multi-disciplinary team and established partnerships with the developers, we anticipate the aims will be achievable, and the results generated from this work will translate into meaningful considerations for residents of these neighborhoods. Moreover, we believe the results will allow us to understand not only how agrihoods affect health and wellbeing, but also how residents engage with them, thereby informing future models for development that are effective for improving health and are economically sustainable.

Given funding and scope of work parameters, this study also has several limitations worth noting. First, the comparison community consists of existing residents, meaning we are unable to capture their baseline prior to moving in, unlike with the agrihood participant sample. Capturing residents as they move into a new development is extremely challenging, and it was not feasible to find a comparison community that was being occupied at the same time as the agrihood. Second, due to budgetary constraints, accelerometer-based physical activity measurement and biological data collection are only feasible among participants in the agrihood community, which may reduce cross-group comparability. Third, the funding support received for this work only covers 13 months, thereby allowing for 6 months of follow-up which may be too short to observe meaningful or sustained behavioral and health changes.

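### Aim 1 is sized and analysed as a two-group comparison, but accelerometer and clinic measures exist only in the agrihood group; only a survey-based contrast can be estimated, and its effect size is not justified

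*Protocol article*

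**What the plan says.** **Aim.** Study aims and approaches sets Aim 1 as: "1) assess short-term changes in dietary intake, physical activity, cardiometabolic health indicators, and social connectedness among Texas residents living in the agrihood compared to" a master-planned neighborhood without agriculture. The end of the Introduction says the same. Cardiometabolic indicators are thus part of the between-neighborhood comparison.

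**Analysis.** Data analysis states that "we will compare the changes in physical activity outcomes" (MVPA, LMVPA, walking, sedentary behavior) between the two groups at three time points. The mixed model has group, time and group-by-time terms. The sentence names no instrument. A later sentence in the same section relates resource variables to device-measured activity.

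**Sample size.** Sample size estimation uses a "Type I error rate alpha of 0.05, power of 0.8 for comparing the means between two groups" and considers MVPA, LMVPA and sedentary time. It concludes: "We estimate a sample size of 129 per group will provide adequate power to detect an effect size of" d = 0.35 for every physical activity outcome. It translates this to 7.9–9.6 min/day for MVPA and 13.3 min/day for LMVPA, and takes attrition from a natural experiment with accelerometer-measured MVPA.

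**Data collected.** Study aims and approaches and Data collection give comparison participants three online surveys and nothing else. The limitations in the Discussion confirm that "accelerometer-based physical activity measurement and biological data collection are only feasible among participants in the agrihood community", and describe the consequence as a possible reduction in comparability between groups. Table 1 places a short physical activity questionnaire in the online survey.

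**The concern.** The design, the power statement and the data collection do not describe the same study. A DiD estimate is the change in one group minus the change in the other. For any outcome recorded in one group only, the second term does not exist. Calling this reduced comparability understates it, because for those outcomes there is no comparison.

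Two things are at stake. First, an uncontrolled before-after change in accelerometer MVPA or HbA1c could be reported under a DiD label as an effect of moving to the agrihood, although season, the move itself, repeated measurement and regression to the mean are not controlled. Second, the 80% power and the min/day detectable differences would be read as belonging to a between-group analysis, while the only such analysis available uses a different instrument from the one the sample-size text appears to have in mind.

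**Working it through.** **1. Reproduce the plan's figures.** Inputs from Sample size estimation: d = 0.35, alpha 0.05 (sidedness not stated; two-sided assumed), power 0.80.

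- n per group = 2(1.960 + 0.842)² / 0.35² = 128.1, rounded up to 129. Power of a two-sided t-test at 129 per group is 0.800. A one-sided test would give 101, so the plan is two-sided.
- Cumulative attrition from the two cited rates: 1 − (1 − 0.2064)(1 − 0.0663) = 0.259. Then 129 / 0.741 = 174.1, rounded up to 175.

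Both stated figures reproduce. The arithmetic is sound; it presumes 129 analysable people in each of two groups.

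**2. Which measures exist in which group?**

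| Measure | Agrihood | Comparison |
|---|---|---|
| Accelerometer MVPA, LMVPA, sedentary time | 3 time points | none |
| Measured blood pressure, HbA1c, lipids, carotenoids, weight | 2 assessments | none |
| Survey, including the physical activity questionnaire | 3 time points | 3 time points |

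**3. Can the interaction be estimated?** With two groups and three times, the fixed effects are intercept, group, two time terms and two group-by-time terms: six columns. With both groups observed the design has rank 6. With agrihood rows only it has rank 3. Group and group-by-time effects are then not identifiable, and power for them is undefined. For survey outcomes the rank is 6 and the DiD can be estimated.

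**4. Does the sample-size basis carry over to the survey?** The stated detectable differences imply SDs of

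- MVPA: 7.9 / 0.35 = 22.6 and 9.6 / 0.35 = 27.4 min/day;
- LMVPA: 13.3 / 0.35 = 38.0 min/day.

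The protocol gives no SD for the questionnaire. The following is therefore an assumption, not a finding: hold the cited effect of 10.4–10.9 min/day fixed and let the self-report SD be a multiple of the implied MVPA SD, with 129 per group and a two-sided t-test.

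| SD multiple (assumed) | SD, min/day | Detectable difference, min/day | Power for 10.4–10.9 min/day |
|---|---|---|---|
| 1 | 22.6–27.4 | 7.9–9.6 | 86–97% |
| 1.25 | 28.2–34.3 | 9.9–12.0 | 68–87% |
| 1.5 | 33.9–41.1 | 11.9–14.4 | 53–73% |

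For example, at multiple 1.5 the lower end is d = 10.4 / 41.1 = 0.253, power 0.53; the upper end is d = 10.9 / 33.9 = 0.322, power 0.73.

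**The case against.** The strongest reply is that the DiD sentence names no instrument. Both groups answer a physical activity questionnaire three times, so a between-group DiD on self-reported activity is available. The phrase about device-measured outcomes belongs to a separate analysis of resource variables. This stands, and it limits the point: a reader might infer that the study has no control group for physical activity at all, and the protocol does not support that. It does not settle the matter, because the sample-size text includes LMVPA, which the protocol does not show the survey to yield, and borrows attrition from an accelerometer study.

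A second reply is that 129 per group holds for any outcome with d = 0.35. That also stands. What lacks support is d = 0.35 itself, and its min/day translation, for self-report. The SD sources cannot be seen here, so that they are device-based is an inference.

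Third, Data analysis specifies no DiD model for the clinic measures, and Life's Essential 8 is a survey measure in both groups. So the fault for cardiometabolic outcomes lies in the wording of the aim, not in a specified model. Survey items do not replace measured blood pressure, HbA1c or lipids.

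Two further readings are tempting but not supported:

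- For Aim 2 the plan says "we will use DiD analysis to explore longitudinal changes for residential time use and engagement outcomes". A reader might infer a DiD on the one-week diary kept by 48 agrihood residents. The text never ties the DiD to the diary, and it says comparison participants will be asked about time spent with their neighborhood's features.
- The sentence "This sample size is adequate to detect effect sizes that are small to medium for all outcomes" might seem refuted by the dietary-recall subsample of 20. The sentence rests on calculations for other aims, and the recall data are only to be examined among agrihood residents; no power is claimed for them.

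**Conclusion.** The contradiction is real and should be resolved before analysis. For accelerometer and measured clinic outcomes the comparison group contributes no observations, so the between-group contrast cannot be estimated and the stated power does not apply to it. The disclosure in the limitations does not repair this, because the aim, the sample-size text and the analysis text were left as they are. This conclusion rests on the protocol's own account of data collection and needs no outside assumption.

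For self-reported activity the DiD can be estimated and 129 per group is correct for d = 0.35, but the relevance of that effect size and of the min/day figures is unsupported. How much power is lost, if any, cannot be determined from the protocol; 53–73% at 1.5 times the SD is an illustration that depends wholly on the assumed multiple and on holding the absolute effect fixed.

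**What to change.** - **Data analysis and Sample size estimation:** name the questionnaire outcomes collected in both groups as the between-group DiD physical activity outcomes. Keep LMVPA as a between-group outcome only if the survey yields it in both groups.
- **Sample size estimation:** re-justify d for those outcomes and restate the detectable differences with a self-report SD and its source. The claim "D = 0.35 for all physical activity outcomes" should be limited to the outcomes so justified.
- **Accelerometer and mobile-clinic measures:** analyse as change within the agrihood group, with no between-group or causal claim.
- **Aim 1 (Introduction, Study aims and approaches, Discussion):** reword so that the neighborhood comparison covers survey outcomes, and device and clinic measures are described as agrihood-only. State in the limitations that the contrast is absent for these measures.

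The cost is revised wording and one repeated power calculation, with no new data collection. The sponsor gives up the between-group claim for device and clinic outcomes and will probably have to state a less favourable detectable difference.

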#### Inclusion criteria

All participants will be adults, some of whom may be from the same household, and pregnant women may also be included. Specific inclusion criteria are below.

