Additional challenges may arise with retention from recruitment events to follow-up in-person physical assessments. The MHACs are based in Dallas, Texas, and our team has limited days for on-site biological data collection, which may create scheduling barriers. To mitigate this, participants will be offered flexible options such as completing online surveys remotely and receiving accelerometers by mail or at a designated community pick-up location (the Filling Station). Higher-than-usual attrition was anticipated and accounted for in our study design. The protocol also allows for multiple adults (e.g., married couples) within the same household to participate. This decision was made to help achieve recruitment and enrollment goals given the number of households under contract. Interclass correlations within households will be accounted for statistically in the analysis.

For cholesterol and HbA1c data, we are using finger prick sampling rather than venipuncture. Although venipuncture is often considered more precise, capillary testing has been shown to produce comparable results when performed properly and is substantially less invasive and more acceptable in community-based research settings (41–45). Self-reported survey data also introduce potential recall and social desirability bias. The economic analysis component is exploratory, drawing on developer-provided data and resident perceptions. While this approach supports early feasibility insights, it limits the ability to conduct standardized cost–benefit or return-on-investment modeling. Future work will incorporate objective financial metrics (e.g., property values, healthcare cost offsets) to strengthen policy and planning relevance.

Finally, this study is limited to one agrihood in a single region (Fort Bend County, Texas), which may restrict generalizability to other cultural, climatic, or socio-economic contexts. Despite these limitations, this pilot study represents a critical first step in establishing the feasibility, logistics, and interdisciplinary partnerships needed for more rigorous future work. The present phase provides foundational data to inform a larger, multi-site randomized controlled trial with extended follow-up, expanded objective data collection, and greater diversity among participants.

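### The model's neighborhood random effect coincides with study group and cannot be estimated, while the household correlation promised in the Discussion appears in neither the stated model nor the sample size

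*Protocol article*

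**What the plan says.** The Data analysis section of the protocol article specifies linear mixed models with fixed effects for group, time and their interaction, covariates, a participant random effect, and one further random effect: "Random cluster effects will be included to account for correlations between participants in the same neighborhood". The same strategy is reused there for the dietary outcomes and for Aim 2. The Abstract and the Design and setting section describe one agrihood and one comparison neighborhood.

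On households, the Inclusion criteria say: "All participants will be adults, some of whom may be from the same household". The Discussion gives married couples as an example, explains that this helps to reach enrollment goals, and adds: "Interclass correlations within households will be accounted for statistically in the analysis". It names no method.

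On size, the Sample size estimation section says: "we calculated sample size for a Type I error rate alpha of 0.05, power of 0.8 for comparing the means between two groups", and then: "We estimate a sample size of 129 per group will provide adequate power to detect an effect size of Cohen’s D = 0.35". It cites an earlier natural experiment that "found a 20.64% attrition rate from baseline to year 1 and a 6.63% attrition rate from year 1 to year 2", and gives deliberately overestimated attrition as the reason for recruiting 175 per group. It mentions neither an intraclass correlation nor a design effect.

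**The concern.** Two things do not fit together.

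First, a random effect for neighborhood needs several neighborhoods per group. With one in each, neighborhood and group are the same variable. The model would then appear to have allowed for neighborhood correlation when it had not.

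Second, the clustering that this design can handle is by household. Couples who share meals and outings are likely to change together. The Discussion commits to dealing with this, but the model in Data analysis contains no term that would do so. If that model were fitted literally, group-by-time standard errors would be too small whenever changes within a household are positively correlated. Whatever the analysis does about households, the stated 80% power was computed as if all participants were independent.

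**Working it through.** **1. Neighborhood term.** With three time points, the fixed-effect matrix (intercept, group, two time indicators, two interaction columns) has rank 6. Adding indicators for the two neighborhoods leaves the rank at 6. Neighborhood is fully aliased with group, so the data carry no information on its variance. Adding neighborhood-by-time indicators also leaves the rank at 6, so neighborhood-specific change is likewise inseparable from group-by-time.

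The effect on standard errors was checked with illustrative variances: participant 0.5, residual 0.5, 20 people per group.

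| Neighborhood variance | SE of group | SE of group-by-time |
|---|---|---|
| 0 | 0.316 | 0.316 |
| 0.1 | 0.548 | 0.316 |
| 1 | 1.449 | 0.316 |

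A random intercept shared by everyone in a neighborhood cancels from change over time. It affects the group main effect and the stability of the fit, but not the interaction.

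**2. Same argument for households.** A household random intercept also cancels from change. What matters for group-by-time is the correlation of household members' changes, so a useful household term must act on change.

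**3. The plan's own sample size.** For d = 0.35, two-sided alpha 0.05 and power 0.80, two independent means need n = 2(1.96 + 0.842)²/0.35² = 128.1, rounded up to 129 per group (129.1 with the t distribution). The one-sided figure would be 101, so the calculation was two-sided. The plan's 129 is reproduced with no allowance for clustering.

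Compounding the two cited attrition rates gives retention of 0.7936 × 0.9337 = 0.741, and 129/0.741 = 174.1, rounded up to 175. The first rate alone would give 129/0.7936 = 162.5, rounded up to 163. So 175 matches the compounded rates, although the planned rate is not stated.

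**4. Adding households (assumed inputs).** Let p be the share of participants in an enrolled pair and ρ the within-pair correlation of change. Neither is in the protocol; the ranges used are p = 0.25 to 1 and ρ = 0.1 to 0.5, with the same p in both groups. The design effect is DE = 1 + pρ.

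- Power at 129 evaluable per group = Φ(0.35/√(2·DE/129) − 1.96)
- Detectable d at 80% power = (1.96 + 0.842)·√(2·DE/129)
- Type I error if households are ignored = 2[1 − Φ(1.96/√DE)]

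| p, ρ | DE | Power, d = 0.35 | Detectable d | Type I error if ignored |
|---|---|---|---|---|
| independent | 1.00 | 80% | 0.35 | 5.0% |
| 0.25, 0.1 | 1.025 | 79% | 0.35 | 5.3% |
| 0.5, 0.3 | 1.15 | 75% | 0.37 | 6.8% |
| 1, 0.3 | 1.30 | 69% | 0.40 | 8.6% |
| 1, 0.5 | 1.50 | 63% | 0.43 | 11% |

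If only the 20.64% rate applied, 175 × 0.7936 = 138.9 would remain per group, and the middle case (DE 1.15) would have power of about 78%.

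**The case against.** The strongest reply is that the Discussion already commits the analysis to handling household correlation, and that a condensed article may leave the method to a fuller plan. That stands. A reader might infer that type I error will exceed 5%. The document does not support this: the last column of the table applies only if the Data analysis model is followed literally and the Discussion's commitment is not carried out, or is carried out only with a household intercept.

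A reader might also infer that the neighborhood term distorts the main result. It does not, because it drops out of group-by-time. Confounding of neighborhood-specific change with the agrihood effect belongs to any design with one site per group, and no random effect cures it. The Discussion does disclose that there is a single agrihood, but only as a limit on generalizability.

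A third tempting inference is that attrition uses up the whole margin between 129 and 175. The planned rate is not stated, the two cited rates cover two years while follow-up here is six months, and partial data from dropouts are kept. With the first rate alone, the remaining 138.9 per group would absorb a design effect of about 1.075 at 80% power.

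Two further points are fair. Pairing may be concentrated in the agrihood, since the reason given for allowing it is the number of households under contract there. The 1.15 case would then average to (1.15 + 1)/2 = 1.075 across groups. Also, d = 0.35 lies below the cited 0.40–0.42; at a design effect of 1.30 and 129 evaluable per group, power is still about 80% for d = 0.40 and 84% for d = 0.42.

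None of this rescues the neighborhood term, which is stated and cannot work with two neighborhoods. Nor does it put a household allowance into the stated power.

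**Conclusion.** The point holds in three parts. The neighborhood random effect is aliased with group, is not estimable and cannot do what the plan says it does; this follows from the design without assumptions. Data analysis and the Discussion disagree on household correlation and must be reconciled. The 80% power for d = 0.35 assumes independent participants, and attrition is the only reason given for recruiting more than 129.

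The size of the power loss depends on assumed inputs. It is negligible if few couples enroll or their changes are weakly correlated (79%), moderate in the middle case (about 75%, or about 78% under year-1 attrition alone), and large only in the extreme case where everyone is in a pair with correlation 0.5 (63%). Inflation of type I error is conditional on how the Discussion's promise is carried out, and is not established.

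**What to change.** - In Data analysis, delete the neighborhood random effect. Alongside the participant effect, specify a household term that acts on change: either a household-by-time random effect or household-clustered robust standard errors. This carries out what the Discussion promises; a household intercept alone would not.
- In Sample size estimation, state an assumed share in couples, an assumed correlation of change and the planned attrition rate, and restate the power or detectable effect with the resulting design effect. In the middle case the detectable d becomes about 0.37.
- State that inference is conditional on these two neighborhoods, because neighborhood-specific change cannot be separated from the agrihood effect.

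The cost is revised wording, a household identifier in the data set and a slightly less favorable power statement. Holding 80% power by recruitment instead would take 180 to 263 per group over the assumed range (175 × DE, rounded up). Restating the power avoids this and adds no participants.
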